### 2.2. Multi-Omics Evaluation

The second aim is to undertake an extensive multi-omics, metabolic, and histological evaluation.

Genomics: Germline genetic markers using DNA extracted from peripheral blood samples collected from patients with IBD will be evaluated. A panel of approximately 30 single-nucleotide polymorphisms (SNPs) will be analyzed using TaqMan allelic discrimination assays [73]. The list of SNPs to be evaluated will be selected by reviewing the available literature of genes involved in immune and inflammatory processes. Univariate and multivariate stepwise logistic regression models will be used to identify the variables associated with CVD risk and MACEs in patients with IBD.

Transcriptomics: Genome-wide expression profiling of mRNA will be conducted using RNAs extracted from tissue samples collected before and after treatment of selected patients to identify pivotal and critical genes associated with therapy response. The designed whole-transcript array used will provide the most accurate, sensitive, and comprehensive measurement of protein coding and long intergenic non-coding RNA transcripts [74]. Gene expression microarray analysis and functional enrichment analysis of the sample data will be performed to reveal abnormally expressed genes at the tissue level and to elucidate the biological significance of the differential expression pattern.

Metagenomics: A comprehensive sequencing of the gut microbiome will be performed. DNA will be extracted from stool samples at baseline and after 2 years of follow-up, and the variable V3 and V4 regions of the 16S rRNA gene will be sequenced. All procedures will follow extensively validated protocols to perform accurate taxonomic and functional profiling of the microbiome composition using newly developed custom bioinformatics and statistical tools [75].

Proteomics: To perform proteomic profiling of plasma samples at baseline and at the end of follow-up, cutting-edge technology will be applied to overcome the limitation of the outstanding dynamic range of plasma proteins [76]. With these targeted proteomic approaches, we will analyze the potential modulation of proteins involved in the most relevant physio-pathological pathways, including inflammation, immune response, and metabolic dysregulation.

Metabolic evaluation: In addition to the standard laboratory evaluation of the glyco-metabolic axis, patients with IBD will be assessed with Fibroscan at the time of enrollment and at the end of follow-up for the presence of hepatic steatosis.

Histology: The biopsy samples will be oriented on acetate cellulose filters, fixed in formalin, and embedded in paraffin. Sections stained with hematoxylin and eosin (H&E) will be used to evaluate the histological activity with standard validated scores. In addition, Claudin-2 immunohistochemistry will be performed on 4 um sections using the Claudin-2 antibody (Cell Signaling Technology, E1H90 clone, 1:100 dilution). The primary antibody will be detected using a biotin-free polymeric horseradish peroxidase (HRP)–linker antibody conjugate system with heat-induced epitope retrieval using the Bond III automated immune-stainer. Claudin-2 expression will be evaluated with a semi-quantified score along the cytoplasmatic cell membranes of the glandular epithelium and/or of the surface epithelium [77].

### 2.3. Prospective Evaluation

At the end of the 2-year follow-up, all patients in the IBD cohorts and the control population will be re-evaluated in terms of CVD risk using SCORE 2, the standard laboratory and cardiologic investigations will be repeated, and the occurrence of new MACEs will be reported. All patients with IBD will be regularly evaluated during the follow-up at 3–6 month intervals, and all will receive a clinical, endoscopic, and histologic evaluation at the end of follow-up. The subgroup of patients with the occurrence of MACEs and those with clinical and endoscopic remission will also repeat the transcriptomics and metagenomics evaluation.

### 2.4. Objectives of the Study

The primary objective of the study will be to evaluate the basal CVD risk in our IBD population compared with the age- and gender-matched cohort of non-IBD patients.

The secondary objectives will be as follows:–Correlation of the basal CVD risk with multi-omics biomarkers, disease activity, lifestyle (i.e., diet, smoking) and therapy;–To evaluate the occurrence of MACEs at the end of follow-up in the patients with IBD and control populations;–To investigate the possible correlation between high CVD risk and MACE occurrence with multi-omics findings;–To identify possible biomarkers of increased CVD risk compared with the control population;–To establish possible correction factors to apply to the standard traditional CVD risk score to incorporate the IBD inflammatory burden.

### 2.5. Statistical Analysis

In this study, a combination of descriptive and inferential statistical methods will be required to ensure robust analysis. For descriptive statistics of the key characteristics of the study (CD, UC, and matched controls), we used the mean and standard deviation (for continuous variables such as age and BMI), median and interquartile range (for skewed variables), and counts and percentages (for categorical variables, such as sex and smoking status). To check the balance between the groups, the standardized mean differences (SMDs) will assess the balance of covariates between the groups. An SMD < 0.1 typically indicates good balance. *t*-tests or Mann–Whitney U tests (depending on normality) for continuous variables will compare means or medians across groups. Chi-square tests or Fisher’s exact tests for categorical variables will compare proportions across groups. In view of the evaluation of the outcome of MACEs, we will use Kaplan–Meier survival analysis to estimate the time to the cardiovascular event, stratified by subgroups. In addition, a Cox proportional hazard regression will allow for evaluation of the hazard ratio (HR) of MACEs while adjusting for confounders. The log-rank test will compare the survival curves between the different groups. We will also apply a multivariate logistic regression evaluating the outcome as binary (e.g., MACEs occurring vs. not occurring during the study period). To ensure the robustness of our findings, sensitivity analyses, such as propensity score matching sensitivity may be performed. Because missing data is common in prospective studies, multiple imputation methods will be used to handle missing data in covariates or outcomes.

The power of our sample was estimated by Cohen’s h effect size for proportions based on different hypotheses about the annual incidence rate of main MACEs in Italy (ISTAT—National Institute of Statistics), a range from 1% to 5% per year, and the estimated increase in cardiovascular events in the Crohn’s disease and ulcerative colitis groups, a range from 1.25 (25% increase) to 3.5 (250% increase). Under the assumption of an incidence rate of 1% per year in the control population, a sample size of 300 patients with IBD (CD and UC) and 300 matched controls will have 80% power to detect an HR of 2.5 or greater. Under the assumption of an incidence rate of 5% per year, there will be approximately 80% power to detect a hazard ratio equal to 1.6. The recruitment period was set to 1 year with 4 years of follow-up (2 years retrospective and 2 years prospective) for a total duration of 5 years. The significance level was set at 5%. A dropout of 5% in both groups is assumed. Effect size parameters: Follow-up period of 3 years retrospectively and 2 years prospectively; alpha (α) of 0.05 (standard significance level); power (1—β) of 90%.

For genomics, logistic regression and generalized linear models will be used for association analyses between the identified genetic variants and clinical outcomes, adjusting for confounders, such as age, sex, and disease duration.

Transcriptome data will be analyzed for differential expression patterns, with statistical significance assessed through empirical Bayes methods, followed by pathway enrichment analysis using gene set enrichment analysis (GSEA) and functional network mapping through tools such as STRING (consortium 2024) or Cytoscape (ver. 3.10.3).

Microbiome data will undergo community profiling through alpha and beta diversity metrics, and associations with clinical endpoints will be tested via multivariate analysis methods, such as canonical correspondence analysis (CCA) and redundancy analysis (RDA). Furthermore, metagenomic functional profiles will be reconstructed using PICRUSt2 or HUMAnN3, allowing for functional comparison across patient subgroups. Integration across omics layers will be realized through data integration analysis for biomarker discovery using latent components (DIABLO) and complemented by machine learning-driven feature selection techniques (e.g., LASSO, elastic-net).

Targeted proteomics will be analyzed by ANOVA and Tukey’s for a multiple comparison test. To evaluate the concordance of histological evaluation (active/remission) of different scoring system and Claudin 2 immunostaining, Cohen’s kappa (k) will be evaluated.

In addition, to carry out the systematic evaluation of the large, multidimensional dataset, overcoming the limitation of sample size and length of follow-up, and to detect unexpected pathogenetic hypotheses and biomarkers, an artificial intelligence model will be implemented [78]. This will be performed with the use of the Agora Labs platform. Agora^®^ Node supports the training of machine-learning and AI algorithms in a localized or federated architecture, thus allowing multivariate analysis to correlate clinical and multi-omics findings and other attributes included in the study, as well as deeper evaluation of multidimensional datasets by applying random forest (RF) and support vector machine (SVM) models, among others. Random forest (RF) and support vector machine (SVM) models, specifically, will be tested on feature selection tasks and on the identification of predictors of cardiovascular events from clinical and multi-omics data. RF will highlight influential factors (e.g., genetic markers, microbiome composition, and inflammatory markers), which will then be prioritized in subsequent modeling stages. SVMs, known for their performance with smaller datasets, will then refine classification based on selected features, creating a baseline model for cardiovascular risk. Neural networks, particularly deep neural networks (DNNs) or convolutional neural networks (CNNs), will also be tested in the handling of the study’s complex, high-dimensional dataset, especially in identifying non-linear relationships across genomics, transcriptomics, and proteomics data. After RF and SVM have highlighted the most predictive features, these will be integrated into neural networks to improve accuracy in predicting cardiovascular events.

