
The control cohort will be that of the CV-PREVITAL trial (a multicenter, prospective, randomized, controlled, open-label interventional trial—NCT05339841) designed to compare the effectiveness of an educational and motivational mobile health (mHealth) intervention versus usual care in reducing CV risk. The Cardiology Unit of IRCC Policlinico San Donato has already enrolled 1109 healthy individuals in this trial. These participants, who were free from known CVDs at baseline, have already completed a 1-year follow-up and are still under cardiological evaluation to monitor their CV health over time. The control group for the IBD cohort, matched for age and sex, will be extrapolated from this population.

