### 3.2. Characteristics of the Control Population

Table 3 reports the basal characteristics of the control population enrolled in the study CV PREVITAL. The enrollment of this cohort is complete, and all subjects underwent evaluation of their CV risk score and provided blood samples at baseline to evaluate total cholesterol and its fractions, fasting glucose, glycate hemoglobin, triglycerides, homocysteine, and C reactive protein. In addition, bio-samples were collected for further possible multi-omics evaluation and carotid intima-media thickness (IMT) evaluation by Doppler ultrasound. By applying the propensity score from this cohort, an age- and gender-matched control population will be selected for comparison with the IBD cohort.

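### The primary comparison uses controls matched on age and sex, but the tests named for it ignore age and sex, so it is conservative and gives up precision by an amount the article does not let one fix

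*Protocol article*

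**What the plan says.** **Design.** Section 2.1 takes the controls from the CV-PREVITAL participants at the same institution: "The control group for the IBD cohort, matched for age and sex, will be extrapolated from this population". Section 3.2 adds how: "By applying the propensity score from this cohort, an age- and gender-matched control population will be selected for comparison with the IBD cohort". The primary objective in Section 2.4 is to "evaluate the basal CVD risk in our IBD population compared with the age- and gender-matched cohort of non-IBD patients". The article does not name the outcome variable there, but Sections 2.1, 2.3 and 5 use SCORE2 as the measure of risk.

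**Analysis.** Section 2.5 checks balance by standardized mean differences and then names the between-group tests. For continuous variables these are t-tests or "Mann–Whitney U tests (depending on normality) for continuous variables will compare means or medians across groups". For categorical variables, chi-square or Fisher's exact "tests for categorical variables will compare proportions across groups". For MACE, a secondary objective, "The log-rank test will compare the survival curves between the different groups", and a Cox model is planned for "evaluation of the hazard ratio (HR) of MACEs while adjusting for confounders", together with a multivariable logistic model. No adjusted, stratified or paired analysis is named for baseline risk.

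**Sample size.** The only power statement concerns MACE: "a sample size of 300 patients with IBD (CD and UC) and 300 matched controls will have 80% power" for a hazard ratio of 2.5 at a control rate of 1% per year. No power is given for the primary comparison.

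**The concern.** Age and sex are matched because they bear on cardiovascular risk. Table 1 lists age as a traditional risk factor, and the risk cut-offs in Section 2.1 change with age. Once the groups are alike on these two factors, the factors no longer contribute to the random difference between group means. An independent-sample test does not know this and puts their whole spread into the standard error. The interval is then wider than the design warrants, and the true error rate lies below the nominal 5%.

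At stake is the main result of the study. A real difference in baseline risk could be reported as no difference, although the data needed to show it were collected.

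The normality rule adds a smaller point. A skewed risk percentage will tend to go to the Mann–Whitney test, which does not by itself give a ratio or difference in risk.

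**Working it through.** **1. The plan's own figure.** Inputs from Section 2.5: 300 per group, alpha 0.05 (taken as two-sided), Cohen's h, 4 years of follow-up.

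- Control rate 1% per year, HR 2.5: p1 = 1 − exp(−0.04) = 0.0392; p2 = 1 − exp(−0.10) = 0.0952. h = 2·asin(√0.0952) − 2·asin(√0.0392) ≈ 0.229. Power = Φ(0.229·√150 − 1.96) = 79.9%, against the stated 80%.
- Control rate 5% per year, HR 1.6: p1 = 0.1813, p2 = 0.2739. Power is 77.6% by Cohen's h and 78.4% by Schoenfeld's formula, against the stated approximate 80%.

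The figures reproduce. They treat the groups as independent and concern MACE, so they say nothing about the primary comparison.

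**2. Effect of leaving out age and sex.** Let R² be the share of variance of the (log) risk score due to age and sex in the matched sample. With close matching this equals the within-pair correlation.

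- Standard error used divided by the true one: 1/√(1 − R²)
- True size of the nominal 5% test: 2·[1 − Φ(1.96/√(1 − R²))]
- Power of the unadjusted test where the adjusted one has 80%: Φ(1.96 + 0.84 − 1.96/√(1 − R²))

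R² is not in the article, so the first column is an assumption:

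| R² | SE too wide by | True size | Power (80% if adjusted) |
|---|---|---|---|
| 0.1 | 1.05 | 3.9% | 77% |
| 0.2 | 1.12 | 2.8% | 73% |
| 0.3 | 1.20 | 1.9% | 68% |
| 0.5 | 1.41 | 0.6% | 51% |
| 0.6 | 1.58 | 0.2% | 38% |
| 0.7 | 1.83 | 0.03% | 22% |

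Power falls below 40%, half of the 80%, only from R² of about 0.59.

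**3. Where R² might lie.** Table 3 gives the age SD of the control pool (6.5 years) and its sex split (492 men of 1109, 0.444). Assume that log SCORE2 rises by 0.075 per year and is 0.5 higher in men. The variance due to age and sex is then (0.075·6.5)² + 0.5²·0.444·0.556 = 0.238 + 0.062 = 0.299. The remaining SD decides the rest:

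- SD 0.4: R² = 0.299/(0.299 + 0.16) = 0.65; SE 1.69 times too wide. For a 10% higher score in IBD, power is 34% unadjusted against 83% adjusted.
- SD 0.6: R² = 0.45; 1.35 times; 80% becomes 56%.
- SD 0.8: R² = 0.32; 1.21 times; 80% becomes 66%.

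Weaker slopes (0.05 and 0.3) with SD 0.4 to 0.6 turn 80% into 57% to 70%. Over a wider set of assumed models, the correlation ran from about 0.10 to 0.85. Slopes and residual SDs are all assumed, and the age SD is that of the pool, not of the matched sample.

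**4. Against an unmatched study of the same size.** Take the standardized difference of 0.229 that independent groups of 300 detect with 80% power. With matched groups, the unadjusted test has 80% power at correlation 0, rising to 94% at 0.7. The adjusted test rises from 80% to 99.9%. The unadjusted test thus forgoes a gain but loses nothing.

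**5. MACE.** For a binary event, the within-pair correlation in the same kind of model was 0.01 to 0.12, which makes the standard error 1% to 7% too wide.

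**The case against.** - **A condensed article.** The sentence naming the tests follows the descriptive statistics and balance checks and does not mention SCORE2, and a full protocol or SAP may specify the primary model. It is therefore an inference that these tests serve the primary objective. It is a fair one: no other method is named for comparing baseline risk, while adjustment is spelled out for MACE and for the genomic analyses.
- **The test is valid.** This stands. A conservative test does not produce false positives, and no stated power is lost, because none was stated for this comparison.
- **The size is unknown.** This also stands. A reader might infer that, because the score leans on age and sex, the intervals are far too wide and most of the power is gone. That needs R² of about 0.6 or more. The documents give no R², no slopes, no SD of the score and no matching caliper. At R² of 0.1 to 0.3 the intervals are only 5% to 20% too wide. A large loss is possible but not shown.
- **MACE is already adjusted.** Largely true. A reader might extend the point to the log-rank test, but the adjusted Cox and logistic models are planned and the effect on the standard error is small.
- **Pairs may not exist.** True. Section 3.2 describes selecting a control population by propensity score, and no section says that pairs are kept. Paired tests or stratification by matched set cannot be taken for granted. Regression on age and sex needs no pairs.
- **A rank test does not rule out an effect estimate.** Also true, so the normality rule is a secondary matter.

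**Conclusion.** The point holds as a loss of efficiency, not as an invalid analysis. The design controls age and sex, the named tests for baseline risk leave them out, and the standard error is too large by 1/√(1 − R²) whenever age and sex explain part of the score. For R² from 0.1 to 0.7, intervals are 1.05 to 1.8 times too wide, and 80% power becomes 77% to 22%. This rests on close balance in age and sex after selection and on the assumed R². The direction is sure; the amount is not. It is a recommended improvement at no cost to the study.

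**What to change.** Add one paragraph to the analysis section:

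- **Primary analysis:** linear regression of log(SCORE2) on IBD status, age and sex, reported as an adjusted ratio with 95% CI, with no normality pre-test. Use standard errors clustered on the matched set only if pairs are formed and kept.
- **Binary baseline risk categories:** logistic regression adjusted for age and sex, in place of chi-square or Fisher's exact test.
- **MACE:** make the already planned adjusted Cox model the main comparison, state that age and sex are in it, and treat the log-rank test as descriptive.

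The unadjusted tests can stay for describing the groups. Age and sex are already needed for the matching, so no new data are required. Section 3.1 reports enrollment in progress, with the full analysis to come after follow-up, so the change can still be specified in advance.

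### The power statement assumes one control per IBD patient, although 1109 scored and followed controls exist; up to 3:1 matching would add precision cheaply, within the limits of age overlap

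*Protocol article*

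**What the plan says.** Protocol article, section 2.5, gives one sample-size scenario: "a sample size of 300 patients with IBD (CD and UC) and 300 matched controls will have 80% power" to detect a hazard ratio of 2.5 when the control rate is 1% per year, and about 80% for a hazard ratio of 1.6 at 5% per year. The method is Cohen's h, an "effect size for proportions based on different hypotheses about the annual incidence rate of main MACEs". No ratio other than 300 to 300 appears.

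Section 2.1 says that the cardiology unit "has already enrolled 1109 healthy individuals in this trial" (the mobile-health trial that supplies the controls), and that these people "have already completed a 1-year follow-up and are still under cardiological evaluation". Section 3.2 adds that recruitment of controls has closed and that "all subjects underwent evaluation of their CV risk score and provided blood samples at baseline". From this pool, "an age- and gender-matched control population will be selected for comparison with the IBD cohort", by propensity score. Neither section states a ratio or an age caliper.

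Section 2.4 makes baseline cardiovascular risk the primary objective and MACE occurrence a secondary one. Section 3 reports 167 IBD patients enrolled so far.

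**The concern.** The scarce group is IBD. Controls are already enrolled, and 300 of 1109 is 27% of the pool. When one group is fixed and the other is already recruited, one-to-one matching is rarely the best use of the data.

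The MACE comparison is short of events, mainly on the control side. At 1% per year over 4 years, 300 controls yield 300 × 0.0392 ≈ 12 events. At a hazard ratio of 2.5, 300 IBD patients yield 300 × 0.0952 ≈ 29. Taking the variance of the log ratio as roughly 1/12 + 1/29, controls contribute about 70% of it, so extra controls act on the larger part.

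The primary contrast would gain too, and the control risk scores it needs already exist. At stake is precision that could be had without recruiting anyone. The validity of the comparison is not in question.

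**Working it through.** **Inputs.** From section 2.5: 300 IBD patients and 300 controls, control rates of 1% and 5% per year, hazard ratios 2.5 and 1.6, α = 5%, and 4 years of follow-up (the first of two windows given). From sections 2.1 and 3.2: 1109 controls. From Table 3: control age 55.9 ± 6.5 overall, 56.9 ± 6.5 for 492 men and 55.1 ± 6.2 for 617 women. Two-sided testing is assumed because it reproduces the stated power. The IBD age distribution is not shown and is assumed.

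**Formulas.** Cumulative risk p = 1 − exp(−rate × T). h = 2·asin√p₁ − 2·asin√p₀. Power = Φ(h·√[n₁n₀/(n₁+n₀)] − 1.96).

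**Step 1: the plan's own figure, T = 4, 300 vs 300.** √(300·300/600) = 12.247.
- 1% per year, HR 2.5: p₀ = 0.0392, p₁ = 0.0952, h = 0.2285. Power = Φ(0.2285 × 12.247 − 1.96) = 79.9%. Stated: 80%.
- 5% per year, HR 1.6: p₀ = 0.1813, p₁ = 0.2739, h = 0.2219. Power = 77.6%. Stated: approximately 80%.

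**Step 2: more controls, all 300 IBD patients matched, T = 4.**

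| Controls | √[n₁n₀/(n₁+n₀)] | 1%/yr, HR 2.5 | 5%/yr, HR 1.6 |
|---|---|---|---|
| 300 | 12.247 | 79.9% | 77.6% |
| 600 (2:1) | 14.142 | 89.8% | 88.1% |
| 900 (3:1) | 15.000 | 92.9% | 91.4% |
| 1109 (all) | 15.366 | 94.0% | 92.6% |

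The gain from 2:1 or 3:1 is about 10 to 14 points. On the 2 prospective years alone, both scenarios start at about 51% and reach about 63% (2:1) and 68% (3:1).

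**Step 3: check against the planned log-rank test.** Simulation (4,000 runs per cell, T = 4) gives 79% at 1:1, 91% at 2:1 and 94% at 3:1 in the first scenario, and 78%, 89% and 93% in the second. Schoenfeld's approximation gives smaller gains (about 4 to 7 points at HR 2.5 and 8 to 14 at HR 1.6, for 600 to 1109 controls). It understates power when the hazard ratio is far from 1 and the groups are unequal.

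**Step 4: primary contrast.** With equal variances, relative interval width = √(1/300 + 1/n₀) / √(2/300). This is 0.866 at 600 controls and 0.816 at 900, so 13% and 18% narrower, again if all 300 can be matched.

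**Step 5: how many can be matched.** Treating control age as normal, 1109 × Φ((40 − 55.9)/6.5) ≈ 8 controls are under 40 and about 202 are under 50. Matching was simulated on same sex and age within 2 years, with an even sex split among IBD patients and assumed IBD ages from 40 ± 14 to 55 ± 12:
- about 145 to 255 of the 300 IBD patients find at least one control;
- 4-year power at 1:1 is about 47% (second scenario, 145 pairs: Φ(0.2219 × √72.5 − 1.96)) to 73% (first scenario, 255 pairs: Φ(0.2285 × √127.5 − 1.96));
- with up to three controls each it is about 62% to 87%.

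The relative gain of about 13 to 15 points survives. The 90% level does not.

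**The case against.** **Discarding.** A reader might infer that some 800 eligible controls will be thrown away. The article does not say so. The 300 is an input to a power statement, and section 3.2 says only that a matched group will be selected. The ratio and caliper may be fixed in a full protocol or analysis plan that is not shown. This stands. What remains is that the only ratio in print is 300 to 300, without a reason, and that the power is stated for it.

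**Size.** A reader might infer that a higher ratio lifts the study above 90% power. Step 5 does not support that. Section 4 describes many IBD patients as younger adults and stresses those under 40, where the pool is almost empty. An IBD patient with no control in range stays unmatched at any ratio.

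**Cost.** One might say that nothing is gained by stopping at 300. That goes too far. Section 2.3 has the control population re-evaluated at 2 years with SCORE2, laboratory and cardiological investigations, so a smaller control group means less work. First matches are also the closest in age, which helps the SMD < 0.1 balance check.

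**Weight.** On a 4-year window the plan reproduces its stated 80% closely, and MACE is secondary. This is a missed efficiency, not an error. The control source is also a randomised trial. If only one arm were used (assumed half, about 554 controls), full-overlap power at 4 years would still be 89% and 87%.

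**Conclusion.** The point holds as a cheap improvement. One control per patient is assumed without a reason, while the pool is almost four times larger, already scored and still followed. By the plan's own method over 4 years, 2:1 or 3:1 matching is worth about 10 to 14 points of MACE power and a 13–18% narrower interval on the primary contrast if all 300 IBD patients can be matched.

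The absolute levels depend on IBD ages, which the article does not show. Under the assumed range, power is about 47–73% at 1:1 and 62–87% at up to 3:1. These figures also rest on constant hazards, two-sided 5%, no dropout, and the 4-year window. Section 2.5 itself conflicts on that window (2 + 2 years, then 3 + 2) and on power (80%, then 90%).

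**What to change.** In section 2.5, and in the selection sentence of section 3.2, replace 300 controls at 1:1 with variable-ratio matching:
- up to three controls per IBD patient from the 1109, exact on sex and within a fixed age caliper;
- a caliper that is not widened to reach the ratio;
- analysis with matched-set weights or stratification by matched set;
- a report of how many IBD patients have no control in range;
- power restated for the numbers of matched patients and controls actually obtained, and for one reconciled follow-up window and power target.

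The cost is wording, a re-run of the power statement, MACE extraction and 2-year re-evaluation for more controls, and slightly looser later matches, which the caliper bounds. No one is recruited. If re-evaluation is affordable for only 300 controls, use the larger matched set at least for the primary baseline comparison, where the scores already exist.
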